## Abstract

**Introduction:**

The first decompensation event of cirrhosis is a critical point of disease progression, and the incidence of further decompensation occurs up to more than 50%. Fuzheng Huayu tablet is used as a classic anti-hepatic fibrosis herbal compound. There is no randomized controlled trial (RCT) combining Fuzheng Huayu tablet with antiviral to prevent the occurrence of further decompensation. The aim of this study was to conduct a prospective randomized, double-blind, placebo-controlled, multicenter study to investigate its safety and efficacy in terms of the risk of further decompensation events in patients with first decompensation, and to fill the gap of evidence-based medicine in this field.

**Methods and analysis:**

This study aims to conduct a prospective, multicenter, double-blind, randomized, placebo-controlled trial. The planned sample size is 432 patients, with the ratio of the Fuzheng Huayu group to the placebo control group being 1:1. Participants will be randomly assigned to the two groups using a stratified block randomization method at the central level. The Fuzheng Huayu group (Fuzheng Huayu tablets combined with conventional antiviral therapy) and the placebo group (placebo combined with conventional antiviral therapy) will be treated for 48 weeks and followed up to 96 weeks. The study period will last for a total of 2 years. The cumulative incidence of further decompensation events within 1-year, the cumulative incidence of recompensation within 1-year, the incidence of liver failure, hepatocellular carcinoma, and liver disease-related deaths will be analyzed.

**Discussion:**

This study will be a prospective, randomized, double-blind, placebo-controlled, multicenter study to investigate the clinical benefit of Fuzheng Huayu tablets in the risk of further decompensation events in patients with first decompensation.

**Clinical Trial Registration:**

Clinical Trials.gov, study ID NCT07017426; International Traditional Medicine Clinical Trial Registry, registration number ITMCTR2025001365.

## Introduction

1

Cirrhosis has a major impact on global health, increasing the risk of death by 5–10 times (Devarbhavi et al., 2023). Hepatitis B virus (HBV) infection is the leading cause of cirrhosis, and the 5-year survival rate of patients with further decompensated cirrhosis is less than 50%. Such patients often face a high risk of death due to complications such as portal hypertension, ascites, and hepatic encephalopathy, and the first decompensated event is a critical point for disease progression (Lee et al., 2021).

The Baveno VII Consensus Conference agreed on a definition of “further decompensation”. However, until now, the concept of further decompensation, with a higher mortality rate and how to reduce the incidence of further decompensation events, has not been supported by objective evidence (Reiberger and Hofer, 2023). A recent study has shown that the incidence of further decompensation in patients with cirrhosis with first decompensation in 5 years is as high as 51.5%, the risk of death reaches 15.6%, the incidence of further decompensation and death within 28 days is 7.3%, and the incidence of liver transplantation was 2.3% (D’Amico et al., 2024). Therefore, clear prevention of the risk of further decompensation in patients with first decompensation is a pressing clinical issue.

Although inhibition of viral replication by nucleoside (acid) analogs delays the progression of cirrhosis, antiviral therapy alone has limited reversal of established liver fibrosis and liver failure (Liaw et al., 2011). Studies have shown that even with a complete virologic response, patients with decompensated disease are still at high risk for continued progression of liver fibrosis and hepatocellular carcinoma, and there is an urgent need to explore combination therapeutic strategies to promote fibrosis reversal (Wang et al., 2022). At present, commercial Chinese polyherbal preparation (CCPP) such as Fuzheng Huayu, Biejia Ruangan, and Anluo Huaxian have exerted good curative effects in the field of anti-fibrosis, but the evidence level in the guidelines is not high (Yoshiji et al., 2021). Therefore, there is an urgent need to carry out high-level evidence-based evidence to provide evidence for traditional Chinese medicine (TCM) in the field of anti-fibrosis and anti-cirrhosis.

Fuzheng Huayu (FZHY) tablets is a classic Chinese medicine compound composed of Salvia miltiorrhiza Bunge [Lamiaceae; Salviae miltiorrhizae radix et rhizoma], Cordyceps sinensis (Berk.) Sacc [Ophiocordycipitaceae; Cordyceps], Schisandra chinensis (Turcz.) Baill [Schisandraceae; Schisandrae Chinensis Fructus], Gynostemma pentaphyllum (Thunb.) Makino [Cucurbitaceae; Gynostemmatis Herba], Pinus massoniana Lamb [Pinaceae; Pini Pollen], and Prunus persica (L.) Batsch [Rosaceae; Persicae Semen] (Table 1, Supplementary Materials 1–4) (Wang et al., 2018). Known as promoting blood circulation and removing blood stasis, nourishing the liver and replenishing essence. The preparation is clinically used to treat liver fibrosis and cirrhosis, and has multi-target mechanisms such as inhibiting the activation of hepatic stellate cells and improving the function of hepatic sinusoidal endothelium (Sun et al., 2022; Zha et al., 2024; Liu et al., 2009). Phase II in China showed that the reversal rate of liver fibrosis with FZHY tablets alone reached 52% (Liu et al., 2005). For patients with HBV-related cirrhosis, clinical retrospective analysis showed that the combination of FZHY tablets and antiviral drugs produced better efficacy and safety compared with antiviral monotherapy (Cheng et al., 2022; Li et al., 2021). At the same time, it was also found that the combination therapy of FZHY tablets and antiviral therapy in retrospective data can reduce the incidence of hepatocellular carcinoma (HCC) (Shi et al., 2023). Overall, FZHY tablets represent a promising comprehensive treatment option for the treatment of chronic liver disease, providing multiple benefits ranging from hepatitis and fibrosis to cirrhosis and HCC prevention. This is a prospective, randomized, double-blind, placebo-controlled, multicenter study to study the clinical evidence-based use of FZHY tablets in patients with first decompensation.

**TABLE 1 T1:** Component of Fuzheng Huayu tablets.

Herbal name	Produced from	Doses (g)
Salvia miltiorrhiza bunge [lamiaceae]	Dry rhizoma	8
Cordyceps sinensis (berk.) sacc. [Ophiocordycipitaceae]	Dry composite	4
Schisandra chinensis (turcz.) baill. [Schisandraceae]	Dry fruit	2
Gynostemma pentaphyllum (thunb.) makino [cucurbitaceae]	Dry aboveground part	6
Pinus massoniana lamb. [Pinaceae]	Dry pollen	2
Prunus persica (L.) batsch [rosaceae]	Dry fruit	2

## Methods and analysis

2

### Investigational medications

2.1

Take Salvia miltiorrhiza Bunge, Prunus persica (L.) Batsch, and Gynostemma pentaphyllum (Thunb.) Makino, add 10 times and 8 times water respectively, decoct twice, the first time is 2 h, and the second time is 1.5 h, the decoction is filtered, the filtrate is combined, and concentrated to a relative density of 1.20 (50 °C–55 °C), let cool, add ethanol under stirring to make the alcohol content reach 70%, sit to precipitate, take the supernatant, filter, and concentrate the filtrate to a relative density of 1.1–1.2 (50 °C–55 °C), spare. In addition, take Cordyceps sinensis (Berk.) Sacc. and Schisandra chinensis (Turcz.) Baill., add 70% ethanol 10 times and 8 times respectively, heat and reflux twice, the first time is 1.5 h, and the second time is 1 h, merge the reflux solution, filter, and concentrate the filtrate to the relative density is 1.1–1.2 (50 °C–55 °C), set aside, then take Pinus massoniana Lamb. and add 50% ethanol 10 times and 8 times, soak twice at 50 °C, the first time is 4 h, the second time is 2 h, merge the leaching solution, concentrate to the relative density is 1.1–1.2 (50 °C–55 °C), merge with the above two spare concentrates, dry, add appropriate amount of auxiliary materials, mix well, granulate, press into a weight of 0.4 g per piece, and wrap in a film coating.

Fuzheng Huayu tablets is composed of six botanical drugs with functions of promoting blood circulation and removing blood stasis, replenishing essence and nourishing liver (Supplementary Material 8). Through modern pharmaceutical technology, the decoctions of Fuzheng Huayu tablets are then extracted, concentrated, dried, blended, granulated and pressed into tablets. Fuzheng Huayu tablets meet the national drug standard [YBZ19332005-2009Z] of the State Food and Drug Administration, and the approval number is [Sinopharm Zhunzi Z20050546].

### Placebo control

2.2

Placebo preparation matched Fuzheng Huayu Tablets in appearance, color, smell, taste, weight and packaging. Herbal extracts or active pharmaceutical ingredients are not included. The same batch of excipients was used throughout the study to ensure consistency, and the inspection report is attached (Supplementary Material 9).

### Trial design and setting

2.3

This is a randomized, double-blind, placebo-controlled, multicenter trial designed to compare the incidence of recurrence of a first decompensation in patients treated with Fuzheng Huayu tablets [4 tablets three times a day] and placebo. Patients will be randomly assigned in a 1:1 ratio to receive either Fuzheng Huayu or placebo. Regular follow-up will be conducted every 12 weeks (Table 2). The flowchart of this trial is shown in Figure 1. Written informed consent was required for all participants before randomization (Supplementary Materials 5, 6). This protocol was prepared in accordance with the Standard Protocol Project, i.e., Recommendations for Intervention Trials (SPIRIT 2025) guidelines (Supplementary Material 7).

**TABLE 2 T2:** The standard process of the form for the plan.

Study period	V1	V2	V3	V4	V5	V6	V7
	(Baseline)						
Study duration (Weeks)	0w	12w	24w	36w	48w	72w	96w
Informed consent Signing​​	●	​	​	​	​	​	​
Medical history taking	●	​	​	​	​	​	​
Physical examination and vital signs	●	●	●	●	●	●	●
Urinalysis	●	○	●	○	●	○	●
Complete blood count	●	●	●	●	●	●	●
Liver fibrosis	●	○	○	○	●	○	●
Liver function	●	●	●	●	●	●	●
Renal function	●	●	●	●	●	●	●
Quantitative hepatitis B surface antigen (HBsAg)	●	○	○	○	●	○	●
Quantitative hepatitis B e antigen (HBeAg)	●	○	○	○	●	○	●
HBV-DNA viral load	●	●	●	●	●	●	●
Coagulation function tests	●	●	●	●	●	●	●
Electrolyte panel	●	●	●	●	●	●	●
Thyroid function tests (TFTs)	●	○	○	○	●	○	●
Serum alpha-fetoprotein (AFP)​​	●	●	●	●	●	●	●
Abdominal ultrasound (US)​​	●	●	●	●	●	●	●
Liver stiffness Measurement (FibroScan)	●	○	●	○	●	●	●
Gastroscopy (for upper gastrointestinal Bleeding)​​	●	●	○	○	●	○	●
Liver biopsy Pathology​​	○	​	​	​	○	​	○
Immune-related biomarkers	●	​	●	​	●	​	●
Adverse events (AEs)	●	●	●	●	●	●	●

“●” indicates items that must be inspected/recorded, and “〇” indicates items that should be inspected/recorded as needed.

**FIGURE 1 F1:**
[figure not shown]
Flowchart of this study. ETV, entecavir; TDF, tenofovir disoproxil; TAF, propafenacortinofovir; TMF, emetinofovir.

### Participant selection

2.4

Participants who meet the following selection criteria will be included in the study: (1) voluntarily joining the group, able to understand and sign informed consent forms; (2) age range: 18–80 years old, gender not limited; (3) HBsAg positive for ≥6 months during screening; (4) complies with traditional Chinese medicine syndrome types: blood stasis obstructing collaterals, liver and kidney deficiency syndrome; (5) the first decompensated event, which meets the diagnostic criteria for decompensated cirrhosis in the “Diagnosis and Treatment Guidelines for Cirrhosis (2019 Edition)”: (a) having diagnostic evidence for cirrhosis; (b) complications related to portal hypertension may occur, such as ascites, esophageal and gastric variceal bleeding, hepatic encephalopathy, hepatorenal syndrome, etc.

We will exclude patients who meet any of the following criteria: (1) merge hepatitis A, C, D, E, and/or HIV infections; (2) merge autoimmune liver disease, alcoholic liver disease, drug-induced liver disease and other liver diseases; (3) patients with combined malignant tumors; (4) history of splenectomy and transjugular intrahepatic portosystemic shunt surgery; (5) individuals with neurological and psychiatric disorders, especially those with a history of depression, anxiety, mania, schizophrenia, or a family history of mental illness (especially those with a history of depression or tendencies towards depression); (6) individuals with severe heart, lung, kidney and other organ disorders; (7) individuals who plan to undergo organ transplantation or have already undergone organ transplantation; (8) pregnant or lactating women or those with fertility plans during the study period; (9) for those who are allergic to tonifying the body and removing blood stasis, nucleoside (acid) analogues, or drugs, or who meet any contraindications in the research drug instructions (10) individuals who have taken traditional Chinese medicine such as Fuzheng Huayu within the past 6 months (11) other situations that have participated in other intervention studies within the previous 3 months or are deemed unsuitable for inclusion by the researchers.

### Recruitment and randomization

2.5

Prior to enrollment, all eligible participants will undergo an informed consent process. The researcher will provide comprehensive information about the purpose of the study, procedures, potential risks and benefits, and the voluntary nature of participation. Prior to providing written informed consent, participants will have the opportunity to ask questions and discuss participation with family members or counselors.

This multicenter study will use stratified randomization to generate a random sequence assigned to two groups. Stratified by center, within each center, participants meeting the inclusion and exclusion criteria will be assigned random numbers in the order of enrollment according to a pre-generated random coding table. A total of 432 drug numbers will be randomized in a 1:1 ratio to the Fuzheng Huayu group or the placebo-control group using stratified block randomization, with center as the stratification factor and a block size of 4. Prior to the start of the study, a statistician will generate the randomized coding table for participants (blinded randomization schedule) using SAS version 9.4. This schedule will be stamped with a special seal, and one copy will be kept at the research center. Another copy, the center code assignment (dispensing version), will be generated and given to the medication administrator. This dispensing version shows only the medication number and a group code (e.g., A/B); the correspondence between the group code and the actual treatment (Fuzheng Huayu or placebo) is concealed and known only to the statistician who holds the master randomization list. Based on this table, the medication administrator will assign medication numbers, and the assignment will be reviewed by another investigator. The administrator will then dispense the medication to the participant, record the date of assignment, and sign and file the form.

### Intervention

2.6

Fuzheng Huayu group: Fuzheng Huayu 3 times a day, 4 tablets each time for 48 weeks. Conventional western medical treatment: symptomatic supportive therapy + antiviral therapy (recommended first-line potent low-resistance nucleoside (acid) analog therapy: entecavir (ETV)/tenofovir disoproxil (TDF)/propafenacort tenofovir (TAF)/emetinofovir (TMF).

Placebo group: in dosage form, shape, color, texture, odor, and dosage, exactly the same as the study drug, but without the active ingredient of the drug, 4 tablets 3 times a day for 48 weeks of treatment. Conventional western medical treatment: symptomatic supportive therapy + antiviral therapy (recommended first-line potent low-resistance nucleoside (acid) analog therapy: entecavir (ETV)/tenofovir disoproxil (TDF)/propafenacortinofovir (TAF)/emetinofovir (TMF).

### Outcomes and measurements

2.7

Outcomes will be measured every 12 weeks the start of treatment to the end of follow-up is 96 weeks, meaning the total follow-up period is 96 weeks.

#### Primary endpoint

2.7.1

The cumulative incidence of further decompensation events is defined as any of the following in cirrhotic patients 48 weeks after the first decompensation: (1) Development of a second portal hypertension - driven decompensating event (ascites, variceal bleeding, or hepatic encephalopathy) and/or jaundice; (2) Recurrent variceal bleeding, recurrent ascites (≥3 large-volume paracenteses within 1 year), recurrent encephalopathy, spontaneous bacterial peritonitis (SBP) and/or hepatorenal syndrome - acute kidney injury (HRS-AKI); (3) In patients with bleeding alone, development of ascites, encephalopathy, or jaundice after recovery from bleeding (not during the bleeding episode); (4) After the first decompensation, the new increase of total bilirubin >51.3 μmol/L (3 mg/dL) was judged as jaundice (de Franchis et al., 2022).

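### The primary endpoint's 48 weeks are counted from the first decompensation, but treatment, visits and outcome measurement are counted from baseline; the plan needs one time origin, at randomization

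*Protocol article*

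**What the plan says.** Section 2.7.1 (Primary endpoint) is the only place that defines the primary endpoint. It counts further decompensation events, "defined as any of the following in cirrhotic patients 48 weeks after the first decompensation". The jaundice component in clause (4) uses the same origin: "After the first decompensation, the new increase of total bilirubin >51.3 μmol/L (3 mg/dL) was judged as jaundice".

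Section 2.4 (Participant selection), inclusion criterion 5, makes that event the entry condition: "the first decompensated event, which meets the diagnostic criteria for decompensated cirrhosis". None of the listed inclusion or exclusion criteria sets a maximum time from this event to randomization.

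Other sections use a different origin. Table 2 in section 2.3 sets week 0 at the baseline visit. Section 2.6 gives study treatment for 48 weeks. Section 2.7 says "Outcomes will be measured every 12 weeks the start of treatment to the end of follow-up is 96 weeks".

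The remaining sections do not settle the matter. Section 2.10 plans on 48-week cumulative incidences without saying when they start. Section 2.11 specifies a Cox model for the primary time-to-event endpoint without naming time zero. No section names randomization as the origin.

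**The concern.** The endpoint clock and the treatment clock agree only for a patient randomized on the day of the first decompensation. For anyone else, section 2.7.1 as written does two things. It closes the window before 48 weeks of treatment are complete, and it opens the window before the first tablet. On a literal reading of clause (4), a bilirubin rise between the index event and randomization would also qualify, because the clause refers back to the first decompensation and not to baseline.

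This is a stated origin that conflicts with the rest of the design, so it is not a detail that the article merely left to a fuller document. Two analysts, one following section 2.7.1 and the other section 2.7, could derive different event counts and event times from the same data.

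The clauses also need to be ordered. In patients whose index event is bleeding alone, clause (3) counts ascites, encephalopathy or jaundice only "after recovery from bleeding (not during the bleeding episode". Clause (1) carries no such limit, and meeting any one clause is enough.

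**Working it through.** **Inputs from section 2.10.** Event proportions at 48 weeks are p1 = 0.537 (herbal preparation plus antiviral) and p2 = 0.675 (antiviral alone). Two-sided α is 0.05, power is 80%, n is 194 per group before dropout and 216 after 10% dropout.

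**Reproducing the plan's figure.** The printed formula gives

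n = (1.96 + 0.842)² × (0.537×0.463 + 0.675×0.325) / (0.138)² = 7.851 × 0.4680 / 0.01904 = 192.9.

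That rounds up to 193; the pooled-variance version gives 196. The stated 194 lies between them. 194/0.9 = 215.6, so 216 per group and 432 in total. The sample-size arithmetic is not in dispute. With 194 per group, the pooled Z-test has power 79.7%.

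**Assumptions for the effect of the clock.** The documents give no lag, so L is varied, and each calculation applies one value of L to all patients. Hazards are taken as constant and matched to the planning rates, which are assumed to run from treatment start:

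- control: λc = −ln(0.325)/48 = 0.02341 per week
- active: λt = −ln(0.463)/48 = 0.01604 per week
- hazard ratio: 0.685

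**Case 1.** Every patient is event-free at randomization, and the window still closes 48 weeks after the first decompensation. Each arm's risk is 1 − exp(−λ(48 − L)). At L = 12, for example, control is 1 − 0.325^0.75 = 57.0% and active is 1 − 0.463^0.75 = 43.9%.

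**Case 2.** Events before randomization also count, at the control hazard in both arms. Control risk stays at 67.5%; active risk is 1 − exp(−λc·L − λt(48 − L)).

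Results with 194 per arm (pooled Z-test):

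| Lag (weeks) | Treated weeks in window | Case 1: active vs control | Power | Case 2: active vs control | Power |
|---|---|---|---|---|---|
| 0 | 48 | 53.7% vs 67.5% | 79.7% | 53.7% vs 67.5% | 79.7% |
| 4 | 44 | 50.6% vs 64.3% | 78% | 55.0% vs 67.5% | 71% |
| 12 | 36 | 43.9% vs 57.0% | 73% | 57.6% vs 67.5% | 52% |
| 24 | 24 | 32.0% vs 43.0% | 61% | 61.2% vs 67.5% | 25% |

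The primary estimate comes from a Cox model, so case 1 was also checked on the event scale. Expected events are 194 × (sum of the two risks): about 235, 223, 196 and 145 at lags of 0, 4, 12 and 24 weeks. The Schoenfeld formula asks for 220 events at a hazard ratio of 0.685. Log-rank power is 83%, 81%, 75% and 63%, the same pattern.

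**Does the effect itself shrink?** In case 1 the hazard ratio stays at 0.685 by construction, and the risk ratio moves away from 1: 53.7/67.5 = 0.80, 43.9/57.0 = 0.77, 32.0/43.0 = 0.74. What is lost is events. Only in case 2 does the risk ratio move towards 1, for example 57.6/67.5 = 0.85 at 12 weeks.

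**The case against.** The best defence is that section 2.7.1 is loosely worded and the authors meant 48 weeks from the start of treatment. Section 2.7, week 0 in Table 2 and the matching 48-week treatment period all point that way. This stands as far as it goes: the article contradicts itself, and it is not certain that the literal rule would be applied. It does not remove the need for a correction, because the only definition of the endpoint still says otherwise.

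Several stronger readings are tempting but not supported.

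- *Second events before randomization will be counted.* Criterion 5 enrols patients at their first decompensated event, so a patient who has already had a second one arguably does not fit. Case 2 is therefore the weaker case. The early closing of the window does not depend on it.
- *The treatment effect is biased or diluted.* The time before randomization is common to both arms, and in case 1 the hazard ratio is unchanged.
- *The planned 80% power rests on 48 treated weeks.* Section 2.10 does not say when its retrospective rates start. If they also ran from the first decompensation, the losses computed here would not follow in this form.
- *The lag is unlimited.* The listed criteria state no limit. A screening window may exist in the full protocol, and short lags cost little in case 1.
- *Any raised bilirubin counts, and clause (1) overrides clause (3).* Clause (4) asks for a new increase and clause (1) for a second event, which softens both points. The reference level and the order of the clauses are still unstated.
- *The Abstract sets a third window.* "The cumulative incidence of further decompensation events within 1-year" is ordinary rounding of 48 weeks.

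**Conclusion.** The point holds as an internal contradiction about the primary endpoint's time origin. Followed literally, section 2.7.1 puts untreated time inside the window and cuts treated time short by the length of the lag. The consequence is fewer informative events and less power, without between-arm bias.

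Under the case 1 assumptions the loss is small at 4 weeks (about 80% to 78%), moderate at 12 weeks (73%) and substantial at 24 weeks (61%). The larger losses in case 2 (71%, 52% and 25%) require events before randomization to count, which the eligibility wording makes doubtful. All these figures rest on assumed lags shared by every patient, constant hazards, and planning rates that run from treatment start. They show a range and do not forecast this trial. The need to fix the origin does not depend on them, since it decides which events and which person-time enter the primary analysis.

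**What to change.** Reconcile sections 2.7 and 2.7.1, and settle the wording before unblinding:

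1. Define the primary endpoint as time from randomization to the first further decompensation event with onset after randomization, through week 48. Name randomization as time zero for the Cox model, the Kaplan-Meier curves and the cumulative incidence in section 2.11.
2. Reference the new increase in clause (4) to the baseline bilirubin. Liver function is already mandatory at the baseline visit in Table 2.
3. State that clause (3) governs clause (1) for patients whose index event is bleeding alone.

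A rule requiring documented resolution of events present at randomization, and time since first decompensation as a covariate, are optional refinements that this correction does not need.

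The cost is wording in the protocol, any matching registry text, and the derivation of the endpoint from the case report form. The sample size stays at 432, and no visit or assessment is added. With the origin at randomization, the planned figures stand (194 evaluable per group, power 79.7%), provided the retrospective rates also run from treatment start. The sponsor should confirm this and state it in section 2.10.
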